## Introduction

Covid-19 disease results from acute SARS-CoV-2 viral infection. Whilst many patients may remain asymptomatic, or suffer self-limiting disease, symptoms persist in some for an extended period. Long Covid “occurs in individuals with a history of probable or confirmed SARS CoV-2 infection, usually 3 months from the onset of COVID-19 with symptoms, and that last for at least 2 months and cannot be explained by an alternative diagnosis” [1]. It spans multiple healthcare challenges, including physical and psychological symptoms and functional impairment that may be episodic for some and unrelenting for others. It has been estimated that up to 12% of non-hospitalised individuals with COVID-19 may have persistent symptoms for more than 3 months [2]. The nature of the illness, together with its prevalence [3], suggests that Long Covid results in a significant individual, health care system, and societal burden [4–9] which may challenge the delivery of effective, high-quality and sustainable care.

Despite a growing patient population, there is no evidence-based treatment or rehabilitation intervention for Long Covid. Further, non-hospitalised patients and assessments of clinical care pathways have been under-represented in the few Long Covid clinical trials or longitudinal cohort studies so far reported [10]. The epidemiology, clinical trajectory, healthcare utilisation and effectiveness of current care for Long Covid are thus poorly documented [11, 12]. Currently in England, there are fewer than 90 specialist Long Covid clinics in which assessment and treatment is informed by NICE guidelines. However, there is evidence that access to such clinics and related care pathways, the nature of those pathways, and patient experience, varies [13]. Research is thus required to inform diagnosis, care, public health strategies, policy planning, resource allocation and budgeting. It is likewise essential to define the usual care pathway in Long Covid clinics, and to understand patient presentation, and the efficacy and cost of care.

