e) **Cohort study—existing data and extended questionnaire**: Patients at a minimum of one site (confirmed as University College London Hospitals NHS Trust, UCLH, and further sites will be identified in the initial site survey detailed in part (a) above) will be invited to participate in a cohort study, including analysis of their retrospective data, and completion of an extended questionnaire. At their initial clinic assessment, patients will be asked to complete a survey of their symptom nature and duration, and outcome measures. This study will aim to collect follow-up data on these measures to evaluate the extent of recovery in clinical and quality of life outcomes including: symptoms and employment status will be documented, and health and symptoms explored though the EQ-5D-5L questionnaire, Fatigue Assessment Scale (FAS), 2-item Patient Health Questionnaire (PHQ-2), and 2-item Generalised Anxiety Disorder (GAD-2) scale. Some additional questions will be asked in the follow-up questionnaire, including additional symptoms and whether symptoms have resolved, as well as asking patients to complete the Work and Social Adjustment Scale (WSAS) and the Perceived Deficits Questionnaire (PDQ5) (outcome measures included in the STIMULATE-ICP RCT).f) **Assessment of Long Covid stigma:** No validated Long Covid stigma scales currently exist. The one used for this study has been developed based on health stigma theory and emerging qualitative evidence of Long Covid stigma. It utilises items from existing scales related to stigmatising conditions (myalgic encephalomyelitis (ME)/chronic fatigue syndrome (CFS), depression and HIV). These items were reviewed by people living with Long Covid both internal (our patient and public involvement and engagement (PPIE) collaborators) and external to this study. As part of the Long Covid follow-up questionnaire in part (e), patients will be asked to complete a stigma questionnaire. This will be analysed along with other routine data to determine the prevalence and correlates of stigma and discrimination.

Additional data will be requested from the clinics, NHS England, NHS Digital and the Office for National Statistics (ONS) in order to:

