#### Data analysis—Components (e), (g) and (h)

We will use statistical analysis and health economic methods to understand the associations between different symptoms, risk factors and Long Covid outcomes. We will investigate frequencies and the predictive value of different investigations and procedures employed in the assessment of patients referred to Long Covid clinics. We will study community, primary and secondary care healthcare utilisation in individuals with Long Covid at the different stages of diagnosis, treatment and management. We will also consider any confounding effect of comorbidities and multimorbidity by including them as covariates in regression analyses.

Data will be analysed to evaluate the extent of improvement in symptoms and health outcomes over time using appropriate methods, including t-tests and ANOVA. This will include, specifically, longitudinal change in EQ-5D-5L (including the accompanying visual analogue scale, EQ-VAS), employment status, FAS, PHQ-2, GAD-2 scales and resolution of previous symptoms. An evaluation of the extent of healthcare utilisation through the care pathway will be made.

Published costs will be applied to resource use to estimate the cost of Long Covid care. Combining the information on the Long Covid clinic provision with what it costs to deliver care at a patient level and estimates of the number of patients who will need Long Covid care, we will calculate the total cost of delivering care in Long Covid clinics in England over one year. In addition, we will describe the distribution of costs across primary and secondary care and the proportion of cost associated with diagnosis, pharmacological and non-pharmacological treatments including physical rehabilitation and counselling.

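### The only analysis named for the symptom list counts resolution of baseline symptoms, so on that outcome fluctuation with no net change can look like improvement

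*Protocol article*

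**What the plan says.** The relevant text is in three places in the Protocol article.

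- **Analysis.** Under Data analysis for components (e), (g) and (h), the aim is to "evaluate the extent of improvement in symptoms and health outcomes over time using appropriate methods, including t-tests and ANOVA". The next sentence gives the content: "This will include, specifically, longitudinal change in EQ-5D-5L" with its visual analogue scale, followed by employment status, FAS and then "PHQ-2, GAD-2 scales and resolution of previous symptoms".
- **Data collection.** Under Cohort study and analysis of accessible data, Design, component (e), the baseline is the initial clinic assessment, at which "patients will be asked to complete a survey of their symptom nature and duration, and outcome measures". The study then plans follow-up on those measures. It adds: "Some additional questions will be asked in the follow-up questionnaire, including additional symptoms and whether symptoms have resolved". WSAS and PDQ5 are introduced in that same sentence, as follow-up items.
- **Course of illness.** The Introduction refers to physical and psychological symptoms and "functional impairment that may be episodic for some and unrelenting for others".

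**The concern.** Every other outcome in the analysis sentence can move in either direction. The symptom-list outcome cannot. Its denominator is the symptoms a patient already had, and each of those can only persist or disappear. A symptom that was absent at the first assessment and present at follow-up does not enter it. The follow-up questionnaire asks about additional symptoms, but the analysis section gives those answers no named use.

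This matters because one objective of the study is to describe patient outcomes under current care. In an illness that fluctuates for some patients, some symptoms recorded at the first visit will be absent later without any overall improvement. A resolution figure reported alone does not separate that from real improvement, and it cannot show a symptom burden that is stable or growing.

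**Working it through.** The article states no figure for symptom resolution, so there is nothing to reproduce. The check has two parts: what the named outcome can register, and how large it could be when nothing has changed on average.

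**1. What the outcome can register.** For one symptom asked at both times there are four possibilities.

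| Baseline | Follow-up | Label | Enters the resolution outcome? |
|---|---|---|---|
| present | absent | resolved | yes, numerator and denominator |
| present | present | persisting | yes, denominator only |
| absent | present | new or returned | no |
| absent | absent | never recorded | no |

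Net change in prevalence is (number new or returned − number resolved) / number of patients. The named outcome uses the resolved count and leaves out the count that would offset it.

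**2. Size under no net change.** *Assumptions:* each symptom has the same prevalence p at both times, and its presence at the two times has within-person correlation rho. Neither value is in the documents.

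- P(present at both times) = p² + rho·p(1−p)
- P(absent later | present first) = 1 − [p + rho(1−p)] = (1−p)(1−rho)
- P(present later | absent first) = p(1−rho)
- Net change = −p·(1−p)(1−rho) + (1−p)·p(1−rho) = 0 for every p and rho

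| p | rho | Baseline symptoms resolved | Absent symptoms newly present | Net change |
|---|---|---|---|---|
| 0.3 | 0.3 | 0.7 × 0.7 = 49% | 0.3 × 0.7 = 21% | −0.147 + 0.147 = 0 |
| 0.3 | 0.5 | 0.7 × 0.5 = 35% | 0.3 × 0.5 = 15% | −0.105 + 0.105 = 0 |
| 0.5 | 0.5 | 0.5 × 0.5 = 25% | 0.5 × 0.5 = 25% | −0.125 + 0.125 = 0 |
| 0.7 | 0.5 | 0.3 × 0.5 = 15% | 0.7 × 0.5 = 35% | −0.105 + 0.105 = 0 |
| 0.9 | 0.9 | 0.1 × 0.1 = 1% | 0.9 × 0.1 = 9% | −0.009 + 0.009 = 0 |

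The first and last rows are the extremes when p and rho each range over 0.3 to 0.9. A simulation with 20 symptoms at p = rho = 0.5 agreed: the resolved share was 0.2495, while the mean symptom count was 10.00 at baseline and 10.01 at follow-up.

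**3. What the other outcomes cover.** A scale that can move both ways has an expected mean change of zero under the same no-change condition. FAS addresses fatigue, PHQ-2 mood, GAD-2 anxiety, and EQ-5D-5L with EQ-VAS general health. WSAS and PDQ5 do not extend this coverage, because the article describes no baseline for either. The rest of the symptom list therefore has no two-way measure named in the analysis.

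**The case against.** The strongest case on the other side is that symptom change does not rest on this one item. The same sentence analyses change in FAS, PHQ-2, GAD-2 and EQ-5D-5L with EQ-VAS, and the Design section presents these as the means of exploring health and symptoms. A stable or worsening cohort could show on them. The list opens with *include*, so a two-way symptom analysis is not ruled out. An article may also leave per-symptom tables to a fuller plan.

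Most of this stands, and it limits the point. A reader might infer that symptoms are measured only through resolution; the scales show otherwise. A reader might also infer that a cohort with no net change will be reported as recovered. The documents do not support that either: nowhere is recovery defined as symptom resolution, and the Design section uses the word for the clinical and quality-of-life measures as a whole.

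Three further cautions are fair:

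- The Introduction says the illness is episodic for some and unrelenting for others, so how common fluctuation is remains unknown.
- The follow-up item asks "including additional symptoms and whether symptoms have resolved". A patient whose symptom comes and goes may answer that it has not resolved even on a good day. The two-snapshot formula may then overstate the effect.
- *Additional symptoms* may mean symptoms that arose after baseline, or symptoms not on the baseline list. The questionnaire is not shown, so this cannot be settled.

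What does not fall is the narrower point. The article goes beyond leaving the symptom-list outcome open: it names one, and names it in one direction. On either reading of *additional symptoms*, the answers have no named place in the analysis.

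**Conclusion.** The point holds for the symptom-list outcome alone. As named, it counts losses of baseline symptoms and cannot register new or returned ones, so fluctuation without net change can look like improvement on that outcome. The direction is clear wherever recorded symptoms fluctuate. The size is not known: 1% to 49% is an illustration under a stationary model with p and rho assumed between 0.3 and 0.9, and it is not an estimate for this cohort. The scales partly offset the problem for fatigue, mood, anxiety and general health, and leave the rest of the list uncovered. This is a weakness in one named outcome that is worth correcting. It does not invalidate the cohort analysis.

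**What to change.** In Data analysis for components (e), (g) and (h), replace the resolution item with *change in symptoms (resolved, persisting, new or returned)*. Then:

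1. For each symptom asked at both times, report the paired net change in prevalence with a 95% CI, beside the proportion of baseline symptoms resolved.
2. Describe symptoms asked only at follow-up separately. They have no baseline and cannot enter a net change.
3. State in the text whether *additional symptoms* means symptoms that arose since baseline or symptoms not on the baseline list, so that it is clear which of the two items above they belong to.

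The Design section already plans a baseline symptom survey and follow-up on the same measures, so this appears to need a change of analysis wording and little or no new data collection. The cost is slightly more analysis and a symptom figure that will look less favourable than resolution alone.

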#### Data analysis—Components (f) and (i)

Demographic and socioeconomic patient data as recorded in or obtained from Long Covid clinics (where available) will be analysed. They will be compared against demographic and socioeconomic characteristics of those with SARS-CoV-2 infection and self-reported Long Covid using the ONS COVID-19 Infection Survey (CIS) data. CIS is a representative national study of infection prevalence.

Where available, we will use the following variables to assess the representativeness of those accessing Long Covid services: age, gender, employment status, occupation, educational attainment, ethnicity, disability status, area-level index of Multiple Deprivation (full and income-domain), general health pre-COVID-19, pre-existing long term medical conditions including mental health conditions, lone parenting, regular care role, household size, insecure/temporary accommodation. Demographic and socioeconomic predictors of clinical outcomes as collected by Long Covid services will be explored.

We will also assess stigma prevalence and correlates using a quantitative Long Covid stigma short questionnaire. This scale is currently being validated in another study (not published- a follow up of a Long Covid community survey [9]). Demographic and socioeconomic correlates using the above variables where available will be assessed to identify characteristics most at risk of stigma. This will include descriptive statistics (means, medians, proportions); univariate comparisons (chi-square test for categorical variables and t-test for continuous variables); multivariable linear and logistic regression modelling.

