### Aims and objectives

The aim of STIMULATE-ICP-CAREINEQUAL is to understand current Long Covid care and who is presenting at Long Covid clinics.

Specific objectives are:

To describe usual care, health outcomes and healthcare utilisation of individuals with Long Covid. This will include describing:
Current usual care of Long Covid at each trial site involved in the STIMULATE-ICP RCTThe burden of illness at presentation to Long Covid clinicsPatient outcomes from current care pathwaysResource utilisation and the cost of current care at the patient and service levelTo assess the extent of inequalities in access to Long Covid care. This will include describing:
Whether patients who are currently accessing Long Covid services are representative of the overall population of people living with Long Covid, and if there are inequalities in access to care and outcomes.The barriers and facilitators to accessing Long Covid diagnosis, care and supportThe nature and extent of stigma and discrimination experienced by Long Covid patients.

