g) **Describe the Long Covid patient population:** Accessible patient data, such as those from the primary care electronic health record, will be analysed to understand the patient population in terms of age, gender, ethnicity, sociodemographic status, health care resource use, clinical and health outcomes.h) **Estimate the resource use and cost of care:** Patient reported data on resource use, costs and time of work, will be valued using published NHS costs (National Reference Costs; PSSRU Unit Costs of Health and Social Care) and other standard reference costs to estimate the overall societal costs of Long Covid care. Additionally, we will use clinic data collected in part (a) to calculate the costs of delivering care in Long Covid clinics and analyse how this varies by clinic and patient demographics.i) **Examine inequalities in Long Covid care:** Routinely collected socio-economic, demographic and health characteristics of patients accessing services will be compared to Office for National Statistics (ONS) data on COVID-19 infections and Long Covid in the community, to estimate representativeness of those reaching Long Covid services.

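### The access comparison sets clinic patients of unstated coverage against a national survey and includes infected people as a comparator, so clinic location and Long Covid risk can pass for, or mask, unequal access

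*Protocol article*

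**What the plan says.** The second objective (Aims and objectives) asks "Whether patients who are currently accessing Long Covid services are representative of the overall population of people living with Long Covid", and whether there are inequalities in access. Component (i), in the Design part of the cohort section, answers this by setting routinely collected patient characteristics against ONS "data on COVID-19 infections and Long Covid in the community", in order "to estimate representativeness of those reaching Long Covid services".

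The section Data analysis—Components (f) and (i) repeats the plan. For the clinic side: "Demographic and socioeconomic patient data as recorded in or obtained from Long Covid clinics (where available) will be analysed". These data will be "compared against demographic and socioeconomic characteristics of those with SARS-CoV-2 infection and self-reported Long Covid using the ONS COVID-19 Infection Survey". Of the survey it says: "CIS is a representative national study of infection prevalence".

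The same section lists 14 variables for judging representativeness. The only area measure among them is the deprivation index; region and clinic catchment are absent. The number of clinics supplying component (i) is not given. The Discussion describes six initial clinics and puts the total in England below 90.

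**The concern.** Two features of the stated comparison let something other than access into the result.

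- **Place.** If the contributing clinics serve only some areas, their patients will resemble the people of those areas. A national reference then shows differences in ethnicity, age or deprivation even if everyone with Long Covid in the served areas is equally likely to reach the clinic. Adjusting for deprivation does not remove regional differences in, say, ethnic mix.
- **Comparator.** The objective concerns people living with Long Covid. People with infection are a wider group: the Introduction estimates that up to 12% of non-hospitalised cases have symptoms beyond 3 months, so on that figure at least 88% do not. A difference from them combines developing Long Covid with reaching a clinic, and the article does not say which contrast will support statements about access.

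This is the only quantitative comparison given for the representativeness question, and policy makers and those who commission Long Covid services are among the named audiences. An inequality that is misjudged in size or direction could therefore affect decisions about services.

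**Working it through.** The article states no sample size, effect or precision for this comparison, so there is no figure to reproduce. The check separates what the contrast measures and then shows its sensitivity. **All shares and ratios below are assumptions, not document figures.**

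**Set-up.** For a given population group, let

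- *r* = ratio of Long Covid risk after infection (group versus others);
- *g* = odds of group membership among Long Covid cases in the served areas, divided by the same odds nationally;
- *a* = ratio of the chance of reaching a clinic, among Long Covid cases in the served areas.

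The odds of group membership among clinic patients, divided by the odds in each reference, are then

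- against infected people nationally: *a × g × r*;
- against Long Covid cases nationally: *a × g*;
- against Long Covid cases in the served areas: *a*.

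Only the last isolates access within the areas served. The factor *g* is part of national access if the clinic data cover all clinics or a fair sample of them. If they come from a chosen few, *g* also reflects which clinics supplied data. Six sites are a little over 6/90 = 6.7% of clinics, since the total is below 90.

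**Long Covid risk (*g* = 1).** Take a group forming 50% of infected people with *r* = 1.5. Its share of Long Covid cases is 0.5 × 1.5 / (0.5 × 1.5 + 0.5) = 0.60.

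| *r* | *a* | Against infected (*a × r*) | Against Long Covid (*a*) |
|---|---|---|---|
| 1.25 | 1.00 | 1.25 | 1.00 |
| 1.5 | 1.00 | 1.50 | 1.00 |
| 2.0 | 1.00 | 2.00 | 1.00 |
| 1.5 | 0.67 | 1.00 | 0.67 |
| 1.5 | 0.80 | 1.20 | 0.80 |

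The first three rows create an inequality, the fourth hides one and the fifth reverses its direction.

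**Place (equal access, *a* = 1; reference is Long Covid cases nationally).** The apparent odds ratio is *g* = [c/(1−c)] / [n/(1−n)], with *c* the local and *n* the national share.

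| National share | Local share | Apparent odds ratio |
|---|---|---|
| 15% | 15% | 1.00 |
| 15% | 20% | 0.2500/0.1765 = 1.42 |
| 15% | 30% | 0.4286/0.1765 = 2.43 |
| 15% | 40% | 0.6667/0.1765 = 3.78 |
| 20% | 10% | 0.1111/0.2500 = 0.44 |

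A reversal is possible here too. With 15% nationally, 40% locally and 25% in the clinic, the share ratio is 25/15 = 1.67 against the nation but 25/40 = 0.63 against the served area.

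The place factor affects both planned contrasts. The risk factor affects only the contrast with infected people.

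**The case against.** Four points on the other side carry weight.

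1. **Clinic coverage may be wide.** A reader might infer that component (i) rests on a few local clinics, or on one London clinic. The documents do not support that. The minimum of one site, with a single London trust confirmed, belongs to the questionnaire cohort in component (e). For components (g) to (i), further data will be requested from the clinics, NHS England and NHS Digital. If coverage turns out near-national, the place argument largely falls away. The article does not commit to such coverage.
2. **The matching comparator is already planned.** Self-reported Long Covid is named, so it cannot be said that Long Covid risk will be misread as access. Showing both references can even help to separate the step from infection to Long Covid from the step to the clinic, provided each is labelled. The analysis wording could also mean one group with both attributes, although the Design text points to two sets of data.
3. **The objective is national.** It asks about the overall population with Long Covid, and a national reference fits that. Replacing it with catchments would hide the disadvantage of people with no clinic nearby, which matters because the Discussion reports clinics suspended in some areas. This stands: a regional comparison should be added, not substituted.
4. **Some silences prove little.** A reader might infer that calendar periods will be mismatched. The article says nothing either way, and a full protocol or analysis plan may settle it. The same holds for survey weights, design-based standard errors and a sensitivity analysis on the 3-month definition. None of these is part of this finding.

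Nor is this comparison the whole quantitative answer to the second objective: predictors of clinical outcomes and correlates of stigma are also to be analysed.

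**Conclusion.** The point holds in a limited form. The article itself names a national survey and includes infected people as a reference for a question about people with Long Covid. It does not say which contrast carries statements about access, and it lists no region variable. Followed as written, regional population mix can enter both contrasts if clinic coverage is partial, and Long Covid risk enters the contrast with infected people whatever the coverage.

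The size cannot be fixed from the document. Over the assumed ranges, equal access can look like an odds ratio from 0.44 to 3.78 through place alone and up to 2.0 through risk alone, and a true ratio of 0.67 can look like 1.00. The place result assumes that contributing clinics differ from the nation in population mix; the Discussion's claim that the six sites reflect the diversity of services does not settle that. The documents do not show that the result will be wrong, only that it can be, and that the plan as stated could not tell. This is an inexpensive improvement, not a fault that defeats the objective.

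**What to change.** Amend the component (i) text in the Design part and in Data analysis—Components (f) and (i) as follows.

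- Name survey respondents with self-reported Long Covid as the reference for statements about access.
- Keep the contrast with infected people, labelled as separate and descriptive, and say that it combines the risk of Long Covid with reaching a clinic.
- Keep the national comparison for how far patients represent the overall Long Covid population.
- Beside it, add a comparison with the survey restricted or standardised to the regions that the contributing clinics serve and, where possible, to the same period. Base statements about access within served areas on this one.
- State which clinics, or which national NHS source, supply component (i).

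The cost is a region field in the ONS data request, best settled before the request is made, and wider confidence intervals from the smaller regional reference. No new patient contact is needed.
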